### Intervention and training

The FCD concept was developed by the project partners in the developmental part of the project in 2017. The principles are described in a concept book and a practical guide. Theoretically, FCD is based on social learning theory, neuroscience, and positive psychology. The focus is on proving positive experiences for families and building relationships. Volunteers should meet the families with a positive attitude and show them that they each are important contributors to the family club. The materials also recommend that volunteers use praise and apply predictability and routines in the family club. The volunteers should create a program for each session and present it to the families. The program should include the following elements: welcome, activity, dinner, goodbye.

A family club is run by a volunteer team comprised of a leader and two-to-five further volunteers. Each club consists of up to nine families who meet every second week for 6 months (12 sessions). The club runs for 6 months at a time to ensure enough time for relationships to grow and to create a predictable structure around the club. In the first months, the focus is getting to know each other whereas there is more focus on building both the internal and external networks in the last part of the intervention. The aim is that an FCD will run for consecutive periods but families and volunteers sign up for 6 months at a time. If participants wish to stay in the FCD for another 6 months after finishing the first 6 months they can. Although each club includes both vulnerable and non-vulnerable families all families must participate on equal grounds.

The FCD is based on the following four principles: (1) Meal community; (2) Play, learning, and togetherness; (3) Support and advice; and (4) Bridging to the civil society and the public sector. Each meeting in the FCD must include the first two principles, i.e. meal and play. The 12 sessions center around seven value posters that can be put on the wall in the room. The seven values are: (1) Fun with smiles; (2) Together but not in line; (3) The time is now; (4) Notice and say thank you; (5) More than me; (6) Courage to dare; and (7) Taste the world. The seven values are explained in the FCD concept book and activities are linked to the seven values.

Most volunteers will participate in a one-day training before the club starts. The training is based on the four principles and seven value posters but also provides volunteers with guidance on e.g. body language, teamwork, and meeting facilitation. Each training includes a presentation by an external presenter on relevant aspects from social learning theory, neuroscience, or positive psychology. For experienced volunteers, the training session consists of more advanced training and team support. All volunteers receive a print of the FCD concept book explaining the core principles of the FCD and with suggestions for activities and games that can be used in the club. They also receive a guidebook with practical information on issues such as teamwork, what is expected of a volunteer, club economy, fundraising, confidentiality, and insurance.

### Wait-list control group

Families who are on the wait-list will be offered participation in FCD after approximately 6 months. We do not expect all wait-list families to participate in FCD in the second period. Some areas will still not offer an FCD at this time and we also expect that some families may not be interested in participating at this time point. Therefore, we will have both families who receive FCD in the second period and families who never receive FCD in the control group. Families in the wait-list control may participate in other volunteer projects.

### Outcomes

Data are collected through web surveys at three time-points: baseline, post-intervention (6 months after baseline), and follow-up (12 months after baseline). Participants receive an e-mail with a direct link to the questionnaire. Reminders are sent by text message and e-mail. If the families need help to fill out the questionnaire a student will call them. Families receive a small gift at each of the three data collections. At baseline, they receive a cookbook for children, at post-intervention, they receive a 150 DKK (~ 20 EUR) electronic gift card, and at follow-up, they receive a 100 DKK (~ 15 EUR) electronic gift card. When signing up the families are informed that they will receive a small gift after completing each questionnaire. Data are collected in a secured online survey database. The trial statistician and the principal investigator will have access to the full dataset.

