### Recruitment

We aim to recruit 200 vulnerable families – 80 to wait-list and 120 to FCD. Participants are recruited through the FCD website, by Facebook adds, by municipal social workers, by local social housing employees, and by direct contact with the local FCD volunteers. The three partner organizations have employed project coordinators to find venues, recruit volunteers, recruit families, handle the website and sign-up, and support volunteers. In most cases, the recruitment process is as follows: (1) A family applies for a specific family club through the website and gives consent for VIVE to contact the family; (2) A project coordinator creates a list with participants; (3) The project coordinator allocates participants to intervention or wait-list control; (4) The project coordinator sends contact information and allocation condition to VIVE; (5) The project coordinator informs VIVE about the starting dates of the family clubs; (6) VIVE sends the first questionnaire (including electronic consent to participate) by text-message and e-mail; and (6) The project coordinator informs participants about allocation. Most families are recruited through the FCD website but some are recruited directly at the local site e.g. through an existing scout unit or the local social housing office. In some cases, families will sign up after the FCD has started.

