### Allocation

Families are allocated to a family club or a waitlist based on a first-come-first-serve principle conditional on their vulnerability classification. Around nine families are allocated to one family club and any extra families will be offered to be on a wait-list for the next round or when another club starts in the area at a later timepoint. The coordinators strive to allocate two or three non-vulnerable families to each family group to make sure that non-vulnerable families are present in all clubs. The coordinators also make sure that families with sufficient Danish language skills are present in each club making it possible for families that do not have Danish as their first language to improve their Danish skills. The discretionary allocation of families, carried out by the coordinators, is made without further regards to family characteristics and thus can be considered as good as random conditional on vulnerability status and Danish language skills. Families that sign up for FCD but live in an area where there is currently no FCD are included in the wait-list control group. Families who have been assigned to FCD are included in the wait-list control group if the start of the FCD is delayed by at least 4 months. Families who have been assigned to FCD but are not able to participate, e.g. because they have other obligations on the assigned day, and families who do not show up for FCD are included in the wait-list control group. The flowchart is presented in Fig. 2.

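### T2 is fixed at 6 months after baseline, but the programme itself takes 6 months and its start may slip by up to 4 months, so the post-intervention survey can fall mid-programme

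*Protocol article*

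**What the plan says.** All references are to the protocol article.

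- **Outcomes**: surveys are taken at "baseline, post-intervention (6 months after baseline), and follow-up (12 months after baseline"). T2 is thus both a fixed calendar point and, by its label, the end of the programme.
- **Intervention and training**: "Each club consists of up to nine families who meet every second week for 6 months (12 sessions").
- **Allocation**: families assigned to FCD are "included in the wait-list control group if the start of the FCD is delayed by at least 4 months". Shorter delays are not mentioned, so those families stay in the FCD arm. Surplus families are "offered to be on a wait-list for the next round or when another club starts in the area at a later timepoint".
- **Wait-list control group**: "Families who are on the wait-list will be offered participation in FCD after approximately 6 months". Uptake is described as happening in the second period and as incomplete.
- **Recruitment**: the order of steps is "5) The project coordinator informs VIVE about the starting dates of the family clubs", and then "VIVE sends the first questionnaire (including electronic consent to participate) by text-message and e-mail". Families learn their allocation after that. The section adds: "In some cases, families will sign up after the FCD has started".
- **Statistical analysis**: outcomes are analysed at T2 and T3 under ITT with multiple imputation, and the 12-month data are described as exploratory.

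No passage ties T1 or T2 to the first or last session actually held.

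**The concern.** The programme takes up nearly the whole T1-T2 interval, so there is little room for a late start. The plan nevertheless foresees delays of months and does not move T2 when they occur. An FCD family whose club slips by 3 months after T1 would answer the post-intervention survey about half-way through.

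The 4-month rule also creates an odd boundary. A family delayed slightly less than 4 months and one delayed slightly more have had about the same number of sessions at T2, yet sit in opposite arms.

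With 12-month data exploratory, and some controls having received FCD by then, T2 carries the main comparison. If it mixes partly treated FCD families with some partly treated controls, the estimate is diluted. A null result could then not be told apart from an outcome measured too early.

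**Working it through.** **1. Slack between programme and survey.** Twelve fortnightly sessions span 11 × 2 = 22 weeks. Six months is about 26 weeks. T2 therefore comes after the last session only if the first session falls within about 4 weeks of T1.

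**2. Sessions received by T2.** Assume T1 is taken at the planned start and the club then slips by d months. Time in the club before T2 is 6 − d months. Sessions are given pro rata, 2 × (6 − d), and by counting fortnightly meetings from the first one.

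| Delay d (months) | Months of club before T2 | Sessions, pro rata | Sessions, counted | Arm under the 4-month rule |
|---|---|---|---|---|
| 0 | 6 | 12 | 12 | FCD |
| 1 | 5 | 10 | 11 | FCD |
| 2 | 4 | 8 | 9 | FCD |
| 3 | 3 | 6 | 7 | FCD |
| 3.9 | 2.1 | 4.2 | 5 | FCD |
| 4 | 2 | 4 | 5 | control |
| 5 | 1 | 2 | 3 | control |

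The control rows apply only if the family then attends the delayed club.

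**3. The plan's own power.** Inputs from Power considerations: 120 FCD, 80 control, SMD 0.35, baseline correlation 0.50. Statistical analysis gives two-sided 0.05. With baseline adjustment, SE = √[(1 − 0.50²) × (1/120 + 1/80)] = √(0.75 × 0.02083) = 0.125. Power = Φ(0.35/0.125 − 1.96) = Φ(0.84) = 0.80. The stated figure of approximately 80% reproduces, and it takes the full 0.35 to be present at T2.

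**4. Illustrative dilution.** Assume benefit proportional to sessions, with 0.35 for the full programme. Let a share f of FCD families be delayed d months, and let a share g of controls have received a fraction e of the programme by T2. The expected contrast is 0.35 × [(1 − f) + f(6 − d)/6 − g·e], and power is Φ(contrast/0.125 − 1.96). Every f, g, d and e below is an assumption.

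| FCD families delayed | Controls exposed | Contrast | Power |
|---|---|---|---|
| none | none | 0.350 | 80% |
| 10% by 2 months | none | 0.338 | 77% |
| none | 10% at 4 of 12 sessions | 0.338 | 77% |
| 25% by 2 months | none | 0.321 | 73% |
| 20% by 3 months | none | 0.315 | 71% |
| 20% by 3 months | 15% at 4 of 12 sessions | 0.298 | 66% |

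For the last row: 0.35 × (0.8 + 0.2 × 0.5) − 0.15 × 0.35 × 4/12 = 0.315 − 0.0175 = 0.2975.

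**5. Late sign-ups.** A family that joins after its club has started may have had sessions before T1, and its T2 may fall after the club's round has ended. The mistiming then runs the other way. The article does not say how baseline is defined for these families.

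**The case against.** The strongest reply is that T1 is not detached from the club. Start dates reach VIVE before the first questionnaire goes out, so a club that starts on schedule is finished, or nearly so, at T2. This stands. A reader might infer that T2 generally catches FCD families mid-programme, but the documents support only that it can, when a start slips after T1. The article also does not define the point from which a delay is measured.

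A reader might likewise infer that wait-list controls are commonly exposed by T2, because the offer comes at about the same time. The text does not support that. Uptake belongs to the second period, Allocation expects most controls to come from areas without a club, and some families never receive FCD. Exposure by this route needs an early place or a late T2 reply and is likely marginal. What remains is the family delayed 4 to under 6 months. That route depends on counting such families as controls: analysed in the FCD arm, they would no longer be exposed controls.

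It is also fair to say that the delay shares are invented, that the harsher scenarios give every exposed control close to the maximum exposure possible by this route, and that dilution does not create a false positive. The Discussion already calls causal conclusions tentative.

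The session log and the planned subgroup by sessions attended help only in part. The log is described as recording dates and participant numbers, and a dose subgroup does not correct the timing of the main contrast. Nor is this simply detail left out of a condensed article: the T2 clock, the programme length and the delay rule are all stated, and together they do not fit.

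**Conclusion.** The point holds in a limited form. The fixed 6-month T2, the 6-month programme and the tolerance of delays under 4 months cannot all be met while T2 is called post-intervention. Following the plan as written can give an outcome measured after as few as 4-5 of 12 sessions in the FCD arm. It can also place some families with up to about 2 months of FCD among the controls.

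The direction is towards no effect. The size cannot be computed from the documents. The illustrations run from 77% down to 66% power, and rest on assumed delay shares, benefit proportional to sessions, T1 at the planned start, and 0.35 read as the effect of the full programme. The power statement itself is not in error.

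**What to change.** Reconcile Recruitment, Allocation, Intervention and training, Wait-list control group and Outcomes, so that the survey clock follows the club:

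1. Send T1 shortly before the club's actual start, and T2 at the end of the family's own round.
2. Use the same T1-T2 interval for wait-list families in the same recruitment round, and send their T2 before any first FCD session.
3. State what a delay is measured from, and how baseline is set for families who join a running club.
4. Record first-session date, T2 date and sessions received by T2 for every family in both arms.
5. Keep the ITT analysis of all observed T2 values as primary. Add a sensitivity analysis that excludes or imputes control T2 values completed after a first FCD session. Making this the main analysis would condition on exposure after baseline and depart from ITT.
6. For rounds already surveyed, report sessions received by T2 and do not present the T2 result as the effect of the full 12-session programme.

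The cost is small for rounds still to be surveyed: the surveys are web-based and coordinators already send start dates to VIVE. The price is somewhat variable T1-T2 intervals, and a shorter one for any control offered a place early. Recruitment began in September 2018 and was due to end in March 2020, before the article appeared in June 2020. For the earlier rounds, therefore, only items 4 to 6 are likely to be possible, and item 4 only as far as dates can be recovered.

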### Measures

Table 1 shows the timing of the administration of measures. Socio-demographic characteristics assessed at T1-T3 include the age of the parent, education, occupation, ethnicity, number of children, child age, household status, housing situation, and household economy.

**Table 1 Tab1:** Timing of outcomes – parents

		T1	T2	T3
**Parent measures**				
Background	Age, gender, language, education	√	√	√
Family	Partner, children	√	√	√
Mental health	Warwick-Edinburgh Mental Wellbeing Scale	√	√	√
Self-efficacy	From general self-efficacy scale	√	√	√
Parental stress	Parental Stress Scale	√	√	√
Family conflicts	Partner, child	√	√	√
Family life	Leisure activities	√	√	√
Family routines	Mealtime, duties, bedtime, homework	√	√	√
Network	Loneliness, practical help, confidants	√	√	√
Parenting competences	From Parent Behavior Inventory	√	√	√
Play	Play with children	√	√	√
Screen time	Parent	√	√	√
Family budget	Worries, budget	√	√	√
Satisfaction	Participation, network		√	
**Child measures**				
Well-being child (< 8)	Well-being	√	√	√
Well-being child (≥8)	Kidscreen 10	√	√	√
Network	Friends	√	√	√
Screen time	Mobile phone, computer	√	√	√
Learning activities	Reading, talking	√	√	√

#### Primary outcome

The primary outcome of the study is the 7-item **Short Warwick-Edinburgh Mental Well-being Scale (SWEMWBS)**. This measure is chosen because it is a relatively general measure of well-being in adults. The SWEMWBS has recently been validated in a Danish sample [50]. A total score is calculated by summing the 7 items and converting the raw score according to a published conversion table. Score range 7–35 for both raw and converted scores. A high score is a better outcome [51]. Cronbach’s alpha is 0.85 on a subsample of the included families.

#### Secondary outcomes

The secondary outcomes include the following measures. It was important to both covers a relatively broad area of outcomes that we believe potentially can be impacted by the intervention but also keep the questionnaire relatively short. Therefore, we have shortened some of the included measures.

**Parent Behavior Inventory (PBI)** is a 20-item measure of parenting behavior of parents of early school-aged children. The PBI includes two subscales with high internal consistency: Supportive/engaged (α = .83) and hostile/coercive (α = .81). The PBI has adequate test-retest reliability (r = .69–.74) in an ethnically diverse sample of mothers. To reduce the total number of items we include 10 items – 5 from each of the two subscales; items 6, 10, 11, 12, 14 for Supportive/Engaged, and items 5, 9, 15, 17, 20 for Hostile/Coercive. The score range is 0–25 for each subscale. A high score is better for Supportive/Engaged, a low score is better for Hostile/Coercive [52]. Cronbach’s alpha is 0.66 for the supportive/engaged subscale and 0.55 for the hostile/coercive subscale in a subsample of the included families.

**The Parenting Stress Scale (PSS)** is an 18-item measure of parenting stress that is rated on a five-point scale (Strongly disagree, Disagree, Undecided, Agree, Strongly Agree). We use the revised Danish version with 16 items where the original items 2 and 11 are left out. The Danish version consists of two subscales: Parental Stress (9 items) and Lack of Parental Satisfaction (7 items). Responses are reversed for the lack of parental satisfaction items and all responses for all items are dichotomized (0–1) before scoring. Total score range 0–9 (Parental Stress subscale) and 0–7 (Lack of Parental Stress subscale). A low score is better for both subscales [53]. Cronbach’s alpha is 0.76 for the parental stress subscale and 0.82 for the lack of parental stress scale in a subsample of the included families.

**The general self-efficacy scale (GSE)** is a 10-item measure of optimistic self-beliefs to cope with a variety of difficult demands in life. To reduce the total number of items we include 3 items (8, 9, and 10). The score range is 3–12 and a high score is better. Cronbach’s alpha for the 3-item version is 0.87 in a subsample of the included families.

**Self-worth** We use 3 items from the HBSC project to measure self-worth. The 3 items are inspired by Rosenberg’s concept of self-esteem. Items are scored from 1 (completely disagree) to 5 (completely agree) and summed. A high score is better [54]. Cronbach’s alpha for the 3-item version is 0.87 in a subsample of the included families.

**Family routine** We use 5 items (1,4,9,11,21) from the Child Routine Inventory (CRI - 39 item version). Item 1,3,4, and 5 are from the Daily Living Routines subscale and item 2 is from the Household Responsibilities subscale. Inspired by the CRI we developed 5 extra items on family routines around mealtimes and language. Items are scored from 0 (never) to 4 (always). The high score is better. Cronbach’s alpha is 0.69 for the daily routines subscale, 0.56 for the family life subscale and 0.49 for the meals subscale in a subsample of the included families.

**Kidscreen-10** is a 10-item measure of child well-being (health-related quality of health). Items are scored from 1 (never) to 5 (always) except for items 1 and 9 (reverse). Items 1 and 2 explore the level of the child’s/adolescent’s physical activity, energy and fitness. Items 3 and 4 covers how much the child/adolescent experiences depressive moods and emotions and stressful feelings. Items 5 and 6 ask about the child’s opportunities to structure and enjoy his/her social and leisure time and participation in social activities. Item 7 explores the quality of the interaction between child/adolescent and parent or carer and the child’s/adolescent’s feelings toward their parents/carers. Item 8 examines the nature of the child’s/adolescent’s relationships with other children/adolescents. Finally, items 9 and 10 explore the child’s/adolescent’s perception of his/ her cognitive capacity and satisfaction with school performance. A higher score is better [55]. Cronbach’s alpha is 0.85 in a subsample of the included families. Kidscreen-10 is used with families where the target child is 8 years old or more. Parents with younger children will receive questions about child well-being from the questionnaire to 2–6-year-old children in the project BørnUngeLiv (boernungeliv.dk). Cronbach’s alpha is 0.64 in a subsample of the included families.

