### Statistical analysis

We analyze the primary and secondary outcomes at post-intervention (T2) and follow-up (T3). We use linear regression for normally distributed outcomes and apply robust standard errors to correct for the correlation between observations participating in the same FCD group. In the case of heavily skewed data, we use non-parametric rank-based tests. To check whether the first-come-first-served principle or the allocation of vulnerable families conducted by the volunteers introduce imbalances in the allocation to FCD and the waitlist control, we test for statistical differences in observable characteristics of the two groups using t-tests. In the analysis of the effectiveness of FCD, the hypothesis tested for each outcome is that the FCD group will score better than the wait-list control group. We test this hypothesis with a binary variable indicating the intervention group. We include variables measured at baseline with indications of imbalances (*p* < 0.1) as control variables and apply two-sided tests with 0.05 significance levels throughout. As all outcomes represent a different aspect of the expected outcome of the intervention we do not consider multiple testing issues. We analyze primary and secondary endpoints according to an intention-to-treat (ITT) principle and handle missing data with multiple imputations. Parametric imputation models are preferred, but in case of severe non-normality or convergence issues, we use predictive mean matching or other non-parametric options. We include the 12-month outcome data for exploratory analyses but can also be used as tools in secondary analyses of missingness. Exploratory analysis of data from all three measurements (T1 - baseline, T2 - 6 months and T3–12 months) will be carried out using mixed-effect regression and possibly latent growth curve analysis. The purpose is to assess the longer-term effects of the intervention and to understand how the psychosocial characteristics of the families involved develop over time. In addition to the primary analysis, we will perform subgroup analyses to examine potential differences between subsets of participants. Hence, we analyze subgroups according to the following characteristics: vulnerability (vulnerable or non-vulnerable families); family composition (single parents or cohabiting parents); the age of target child (< 8 years old or ≥ 8 years old); partner organization (KFUMs Sociale Arbejde, FDF, or KFUM Spejderne); the number of volunteers in the FCD; and the number of sessions attended (dose).

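### The printed Kidscreen-10 scoring rule contradicts the article's own item descriptions: items 3 and 4 run against the stated direction, and probably items 1 and 9 as well

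*Protocol article*

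**What the plan says.** All of this stands in the Kidscreen-10 paragraph under Secondary outcomes in the protocol article, except the last item.

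- The instrument "is a 10-item measure of child well-being (health-related quality of health").
- Scoring: "Items are scored from 1 (never) to 5 (always) except for items 1 and 9 (reverse").
- Items 1 and 2: "Items 1 and 2 explore the level of the child’s/adolescent’s physical activity, energy and fitness".
- Items 3 and 4: "Items 3 and 4 covers how much the child/adolescent experiences depressive moods and emotions and stressful feelings".
- Items 9 and 10 concern the child's "perception of his/ her cognitive capacity and satisfaction with school performance".
- Direction: "A higher score is better [55"].
- Reliability and population (the scale applies from age 8 upwards): "Cronbach’s alpha is 0.85 in a subsample of the included families. Kidscreen-10 is used with families where the target child is 8 years old or".
- Under Statistical analysis, "the hypothesis tested for each outcome is that the FCD group will score better than the wait-list control group".

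**The concern.** Three statements in one paragraph cannot all hold: a never-to-always scale scored 1 to 5, reversal of items 1 and 9 only, and a total on which higher is better. A child who always feels low or stressed scores 5 on items 3 and 4 and so gains points on a well-being scale. A child with the most energy and the most satisfaction with school loses points on items 1 and 9, if those items are worded positively as their descriptions suggest.

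The article chose to print a scoring rule, so this is not a detail left to a fuller document. Each outcome is tested for whether the intervention group scores better, so the keying decides what is tested. Anyone scoring the data from the published rule would obtain a total that mixes well-being with ill-being and understates any real effect.

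**Working it through.** **1. Polarity check, item by item**

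| Items | Described content | Stated keying | High item score means |
|---|---|---|---|
| 3, 4 | depressive mood, stress | not reversed | worse |
| 1 | activity, energy, fitness (with item 2) | reversed | worse, if positively worded |
| 9 | cognitive capacity, school satisfaction (with item 10) | reversed | worse, if positively worded |
| 2, 10 | same content as 1 and 9 respectively | not reversed | better, if positively worded |

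Items 3 and 4 conflict with the stated direction with no assumption about items 1 and 9. For items 1 and 9 the conflict is inferred from their pairing with unreversed items of the same described content. The number of miskeyed items m is therefore 2 at least and 4 on the natural reading.

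**2. Raw score range** (k = 10 items, each 1 to 5)

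Best-off child: 5(k − m) + m. Worst-off child: (k − m) + 5m.

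- m = 0: 50 and 10
- m = 2: 42 and 18
- m = 4: 34 and 26

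**3. Consistency with the reported alpha of 0.85**

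The alpha cannot be reproduced, because no item data are given. It can be compared with what the rule would produce. Assume equal item variances and one common inter-item correlation r under correct keying.

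- r = alpha / (k − alpha(k − 1)) = 0.85 / (10 − 7.65) = 0.362
- Variance of the sum: V = k + r[(k − 2m)² − k]
- Alpha: (k / (k − 1))(1 − k / V)

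| m | V | SD | alpha |
|---|---|---|---|
| 0 | 42.55 | 6.52 | 0.85 |
| 2 | 19.40 | 4.41 | 0.54 |
| 4 | 7.83 | 2.80 | −0.31 |

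To reach 0.85 with miskeyed items and zero correlation between the two blocks, the within-block correlation would have to be about 0.56 (m = 2) or 0.78 (m = 4).

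**4. Effect retained**

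Assume the same true benefit on every item. The raw effect is proportional to k − 2m, and the standardised effect to (k − 2m)/SD.

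- m = 2: raw 6/10 = 60%; standardised (6/4.41)/(10/6.52) = 89%
- m = 4: raw 2/10 = 20%; standardised (2/2.80)/(10/6.52) = 47%

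**5. Power**

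The plan's own figure first (Power considerations: 80 control, 120 intervention, SMD 0.35, correlation 0.50, two-sided 0.05). The standard error is √[(1 − 0.50²)(1/80 + 1/120)] = 0.125, and 0.35/0.125 = 2.80. Power is Φ(2.80 − 1.96) = 80%, as stated.

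For Kidscreen-10, assume one target child per family, a base of 200 and uniform ages over 2 to 12. Five of the eleven age years are 8 or more, so n = 200 × 5/11 ≈ 91, or about 36.4 and 54.5 in the same 80:120 ratio. The standard error is √[0.75(1/36.4 + 1/54.5)] = 0.185. Power from the non-central t distribution:

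- correct keying, SMD 0.35: 46%
- m = 2, SMD 0.35 × 0.89 = 0.31: 38%
- m = 4, SMD 0.35 × 0.47 = 0.16: 14%

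Without the baseline correlation of 0.50, which the article gives for its main power calculation and not for this scale, the figures are 37%, 30% and 12%.

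**The case against.** The best case on the other side has four parts.

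- **Items 1 and 9 are not proven to be miskeyed.** Only domain labels are printed, and a negatively worded item can sit in a positive domain. This stands. A reader might infer that four of ten items are certainly reversed in error; the document supports that as a strong inference only. The pairing with items 2 and 10 favours it, but two of ten is the firm minimum.
- **The data were probably keyed correctly.** An alpha of 0.85 on trial families is far from the 0.54 or −0.31 expected under the printed rule. This also stands. A reader might infer that the outcome has been mis-scored, or that most of any effect is lost. Neither follows: the loss arises only if the printed rule is applied, and with two miskeyed items most of the standardised effect survives. Nor does the alpha prove the reverse, because a high enough correlation within each block could produce 0.85.
- **The power figures rest on borrowed inputs.** The correlation of 0.50 is not specific to this scale, and a miskeyed total might have a different one. The 200 is the recruitment target for vulnerable families, whereas clubs also take non-vulnerable ones. The age distribution is assumed. This stands, so the figures are illustrative.
- **It is one line on one secondary outcome in a condensed article.** This bears on severity. It does not reconcile the statements, which contradict each other within a single paragraph.

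**Conclusion.** The concern holds as a defect in the written scoring rule. Items 3 and 4 are keyed against the stated direction on the article's own description, and items 1 and 9 appear to be.

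If the rule were followed, 20% to 60% of the raw effect and 47% to 89% of the standardised effect would remain, and power would be about 14% to 38% instead of 46%. These ranges assume equal inter-item correlations (r = 0.36), equal response on every item, about 91 children aged 8 or more, an SMD of 0.35 and a baseline correlation of 0.50.

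The reported alpha makes it likely that the text is wrong and that the working key differs from it, but the document does not let a reader confirm this.

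This should be fixed. It touches one secondary outcome, in families whose target child is 8 or older. The primary outcome (SWEMWBS) and the stated 80% power do not depend on it.

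**What to change.** Rewrite the scoring sentence so that items 3 and 4 are reverse-scored. Remove the reversal of items 1 and 9 unless the instrument's wording and manual (the article's reference 55) show that they are negatively worded.

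Then confirm which key produced the alpha of 0.85, check that the analysis code uses the corrected key, and inspect item-total correlations before the analysis; a negative one would expose a miskeyed item.

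The cost is one sentence and a short code check. No new data are needed, and neither the design nor the sample size changes.
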